## Abstract

**Background:**

Our understanding of the etiology, pathophysiology, phenotypic diversity, and progression of Parkinson’s disease has stagnated. Consequently, patients do not receive the best care, leading to unnecessary disability, and to mounting costs for society. The Personalized Parkinson Project (PPP) proposes an unbiased approach to biomarker development with multiple biomarkers measured longitudinally. Our main aims are: (a) to perform a set of hypothesis-driven analyses on the comprehensive dataset, correlating established and novel biomarkers to the rate of disease progression and to treatment response; and (b) to create a widely accessible dataset for discovery of novel biomarkers and new targets for therapeutic interventions in Parkinson’s disease.

**Methods/design:**

This is a prospective, longitudinal, single-center cohort study. The cohort will comprise 650 persons with Parkinson’s disease. The inclusion criteria are purposely broad: age ≥ 18 years; and disease duration ≤5 years. Participants are followed for 2 years, with three annual assessments at the study center. Outcomes include a clinical assessment (including motor and neuro-psychological tests), collection of biospecimens (stool, whole blood, and cerebrospinal fluid), magnetic resonance imaging (both structural and functional), and ECG recordings (both 12-lead and Holter). Additionally, collection of physiological and environmental data in daily life over 2 years will be enabled through the Verily Study Watch. All data are stored with polymorphic encryptions and pseudonyms, to guarantee the participants’ privacy on the one hand, and to enable data sharing on the other. The data and biospecimens will become available for scientists to address Parkinson’s disease-related research questions.

**Discussion:**

The PPP has several distinguishing elements: all assessments are done in a single center; inclusion of “real life” subjects; deep and repeated multi-dimensional phenotyping; and continuous monitoring with a wearable device for 2 years. Also, the PPP is powered by privacy and security by design, allowing for data sharing with scientists worldwide respecting participants’ privacy. The data are expected to open the way for important new insights, including identification of biomarkers to predict differences in prognosis and treatment response between patients. Our long-term aim is to improve existing treatments, develop new therapeutic approaches, and offer Parkinson’s disease patients a more personalized disease management approach.

**Trial registration:**

Clinical Trials NCT03364894. Registered December 6, 2017 (retrospectively registered).

## Background

Parkinson’s disease (PD) is the second most prevalent degenerative brain disease [1]. PD will become even more prevalent in our aging society, with an expected pandemic rise and doubling of the current patient volume by the year 2040 [2]. From a systems-biology perspective, PD is seen increasingly as an umbrella term for a group of underlying disorders that all exhibit unique genetic, biological, and molecular abnormalities, and that are likely to respond differentially to a given therapeutic approach [3]. Although adhering to the concept of PD as a single disorder has been useful for the development of symptomatic treatments, it has hindered progress when applied to the development of new interventions that can decelerate or even arrest disease progression [4]. Moreover, our understanding of the basic etiology, pathophysiology, phenotypic diversity, and progression of PD has stagnated, partly due to the limited patient diversity captured in study cohorts, and partly because patients were not studied in sufficient detail (i.e., limited set of outcomes, or brief follow-up periods). As a result, patients do not receive the best care they deserve, leading to unnecessary disability and to mounting costs for society.

To date, there are no reliable biomarkers that can help to predict the widely varying differences between patients in prognosis, rate of progression, time to development of important milestones (e.g., time to first fall, or time to onset of dementia), or treatment response. Cohort studies evaluating multiple outcomes simultaneously are needed to address the multi-dimensional nature of PD. Although several of such cohorts exist and have already shown their merits [5–12], they all have their limitations. These limitations relate to, e.g., the inclusion of a highly selective patient population (rather than a more real-life population), to the multi-center design (introducing variability in assessments and procedures across centers), the lack of detailed clinical and genotyping baseline and follow-up information, the lack of repeated and advanced neuro-imaging, and the absence of wearable sensors to support the follow-up period.

The Personalized Parkinson Project (PPP) intends to build a cohort that has unique characteristics to overcome the limitations of previous studies. The project will focus on the inclusion of “real world” representative patients with PD, who will undergo extremely detailed phenotyping, including microbiome & inflammation, high-quality repeated neuroimaging with repeated MRI scans and fMRI. All assessments are performed at a single centre and optimal retention strategies will be applied. In addition, we seek to perform day-to-day patient monitoring with a multi-sensor wearable device that allows continuous real-time data collection in the free-living environment during a 2-year follow-up period using a state-of-the-art and convenient wearable device. The PPP aims to identify biomarkers that can assist in predicting differences in prognosis and treatment response between patients. The insights generated by the PPP will pave the way to improve existing treatments, to create new therapeutic approaches, and to develop a more precise and personalized disease management approach. Additionally, the PPP cohort applies unprecedented digital security standards, supporting data sharing with qualified researchers worldwide, allowing them to add their research capacity to further address the main aims of this study.

## Methods/design

### Study design

This is a prospective, longitudinal cohort study involving 650 persons with PD. During a 2-year follow-up period, participants will undergo three extensive annual assessments, and continuously wear a multi-sensor investigational research device (the Verily Study Watch). The 5-year study is being carried out in one academic hospital in the Netherlands (the Radboud university medical center in Nijmegen). Participants will be included between October 2017 and December 2019, or longer until the recruitment target of 650 participants is achieved.

Throughout the study period, a panel of 20 Parkinson patients will advise the research team on aspects of the study. For example, during the preparation phase, the panel advised on the design of the study procedures, on recruitment materials, and on subject retention strategies.

### Study population

Participants are eligible for this study if they meet the following criteria:Parkinson’s disease duration ≤5 years, defined as time since the diagnosis made by a neurologist;18 years of age or older;Able to read and understand Dutch;Willing, competent, and able to comply with all aspects of the protocol, including follow-up schedules and biospecimen collections; andProviding written informed consent.

Patients with co-morbidity are explicitly NOT excluded from participation. Candidates will only be excluded in the case of existing co-morbidities that are sufficiently severe so as to hamper the interpretation of parkinsonian disability. Other exclusion criteria include contraindications to magnetic resonance imaging (MRI), pregnancy or breastfeeding, and/or nickel allergy (as components of the Study Watch contain this metal). For the lumbar puncture additional contraindications are defined, i.e., being treated with an anticoagulant medication or clinical evidence of structural cerebral abnormalities.

To guarantee a balanced study cohort, a stratification inclusion model will be applied, by gender (men/women), age (21–45;46–55; 56–65; ≥66 years) and disease duration (< 2½ years; ≥2½ years). Consequently, half of the cohort will have a disease duration of maximally 2½ years at the moment of inclusion, which will also allow us to the impact of very early signals and markers on disease progression.

### Recruitment and enrolment

In the Netherlands, approximately 40,000 people are diagnosed with PD, with an incidence of 8,000 newly diagnosed patients annually. Recruitment strategies that have proven to be successful in past clinical trials will be adopted [13–16]. First of all, the Dutch national ParkinsonNet, an existing nationwide clinical infrastructure in the Netherlands with 3,200 specialized PD professionals, will bring the study to the attention of its members [17–19]. Next, healthcare providers working in university medical centers and community-based hospitals treating PD patients and the Dutch Parkinson Patient Association, representing over 8,000 Dutch Parkinson patients, will promote the study. Finally, various social media announcements and media appearances will be used to reach the target population. All of those interested in the study will be redirected to the study website (www.parkinsonopmaat.nl), where detailed information can be found, along with an application form.

After application, participants receive at least two personal sessions with a dedicated trial assessor by phone to screen eligibility and provide further information. During these calls, prior to inclusion, the assessor verifies that the participant is competent, by discussing the participant’s decision and reasoning. The assessor can decide to not include a potential participant because of limitations in cognitive status that would keep the person from providing informed consent. If the patient is willing and able to participate, (s)he is invited to return a signed informed consent form by mail to the study center and the date for the baseline visit is booked. Once informed consent is obtained, access to the medical records of the treating neurologist and general practitioner is requested to verify the diagnosis of Parkinson’s disease and check whether or not patients are diagnosed with clear dementia in the eyes of the patient’s own physician. Those participants without a confirmed diagnoses and/or presence of dementia, will not be included, despite initial consent. During the first study visit, prior to the assessments, the trial assessor reconfirms that the patient understands the consequences of participation. During the follow-up visits the assessor will verify the cognitive status of the participants in a similar manner. The informal caregiver can also signal a marked cognitive decline that would hamper the patient’s inability to understand the implications of continued participation. Patients who are no longer able to provide a valid informed consent for participation will be excluded from further follow-up, but the data obtained until that moment will be kept in the central database.

### Study procedures and assessments

Participants visit the study site three times for data collection: an initial baseline visit and two annual follow-up visits. Data collection during each visit takes a full day and can be spread out over a 1.5-day period if desired by the patient. Prior to each visit, study participants will be offered a complimentary hotel stay, thereby reducing the need for patients living far away from the study center to travel long distances in the early morning. Patients arrive at the study site in the morning in a practically defined OFF state, i.e., at least 12 h after having taken their last dopaminergic PD medication.

During the three in-clinic visits, detailed clinimetrics with multiple standardized evaluations for motor, neuropsychological, and other PD-related assessments are performed, while wearing the Verily Study Watch (see Table 1 for an overview). Some of the motor assessments are performed first in a clinically defined OFF state and repeated after the participant has taken the regular first morning dose of medication(s) and has subjectively reached a typical ON state. The medical examination and clinical assessments are videotaped with a static camera and/or recorded for audio signals, unless the subject declines. The video-recording are for local use only and will not be shared within the study. In addition, relevant biospecimens are collected, i.e., whole blood for plasma/peripheral blood mononuclear cells (PBMC)/serum/DNA/RNA, cerebrospinal fluid (CSF), and stool for longitudinal genotypic and phenotypic assays. CSF will be collected only at baseline and after 2 years and is the single optional element of the study protocol. Local anaesthesia will be provided to minimize patient burden and atraumatic needles will be used. Moreover, using advanced MRI, at baseline and after two years, indices of in vivo brain structure and function are obtained, using an extension of the UK Biobank protocol [20, 21]. The PPP MRI protocol captures structural MRI (T1 and T2-weighted imaging, diffusion tensor imaging (DTI) and quantitative susceptibility mapping (QSM)), resting functional MRI (fMRI), and two task-related fMRI studies. The tasks probe both primary brain dysfunction, i.e. basal ganglia dysfunction, as well as cerebral compensatory activity. An additional surface electromyography is performed during MRI scanning to monitor tremor, so artifacts can be removed [22]. Finally, to assess autonomic dysfunction, study subjects wear a Holter monitor during each in-clinic visit (except while being in the MRI scanner), and a 12-lead ECG is performed while the subject is supine. Blood pressure is measured in both supine and standing positions, from which the presence of orthostatic hypotension will be assessed.

**Table 1 Tab1:** Overview of included study measures and scales in the Personalized Parkinson Project

Method	Outcome	Scales	Visit 1 (Baseline)	Visit 2 (1 Year)^b^	Visit 3 (2 Years)^b^	After each visit^c^
Assessed by trial assessor	Motor functioning in OFF^a^ state	- MDS-UPDRS-III (including H&Y stage)	X	X	X	
		- Timed up-and-go test	X	X	X	
		- Standing leg test	X	X	X	
		- Rapid turning test	X	X	X	
		- Pegboard test	X	X	X	
	Motor functioning in ON^a^state	- MDS-UPDRS-III (including H&Y stage)	X	X	X	
		- TUG	X	X	X	
		- MDS-UPDRS-IV	X	X	X	
		- Standing leg Test	X	X	X	
		- Rapid Turning Test	X	X	X	
		- Pegboard Test	X	X	X	
		- Grip strength	X	X	X	
	Neuropsychological symptoms	- MDS-UPDRS-I	X	X	X	
		- MoCa (with alternative versions during follow-up)	X	X	X	
		- Phonemic and semantic Fluency	X	X	X	
		- Brixton Spatial Anticipation Test	X	X	X	
		- 15 Words Test	X	X	X	
		- Benton Judgment of Line Orientation	X	X	X	
		- Letter Number Sequencing	X	X	X	
		- Symbol Digit Modalities Test	X	X	X	
	Activities of daily living	- Modified Schwab and England scale	X	X	X	
	Demographics and lifestyle	- Medical history	X	–	–	
		- Lifestyle exposure	X	–	–	
		- Medication (Parkinson and other)	X	X	X	
		- Non-pharmacologic Treatments	X	X	X	
	Biospecimens	- Stool	X	X	X	
		- EDTA Plasma (DNA)	X	–	–	
		- PAX Gene (RNA)	X	X	X	
		- peripheral blood mononuclear cells (PBMCs)	X	–	–	
		- Plasma (no PBMC)	X	X	X	
		- Serum	X	X	X	
		- CSF	X	–	X	
	Autonomic function	- Holter ECG	X	X	X	
		- 12-lead ECG	X	X	X	
		- Blood pressure (standing and supine)	X	X	X	
	Brain structure and function	- Structural MRI (T1, T2, FLAIR, DTI, QSM)	X	–	X	
		- Functional MRI (resting state, task-related)	X	–	X	
Verily Study Watch	Physiological and environmental parameters	- PPG	Continuous data collection, up to 23 h a day.			
		- ECG				
		- IMU including 3-axis accelerometer and 3-axis gyroscope				
		- EDA				
		- Skin temperature				
		- Relative humidity				
		- Barometric pressure				
		- Ambient light level				
Self reported patient questionnaires	Neuropsychological symptoms	- BDI-II				X
		- QUIP-RS				X
		- Apathy scale				X
		- STAI				X
	Sleep disorders	- SCOPA- sleep				X
		- Epworth sleepiness scale				X
	Quality of life	- PDQ-39				X
		- SF-12				X
	Various	- MDS-UPDRS-II				X
		- SCOPA- aut				X
		- RBD questionnaire				X
		- Wearing-off questionnaire				X
		- New Freezing of Gait Questionnaire				X
		- Radboud Oral Motor Inventory				X
		- Screening Questionnaire on Visual Impairment				X
		- PASE				X
Self reported caregiver questionnaires	Burden	- CSI				X

*BDI* Beck Depression Inventory, *CSF* Cerebro-Spinal Fluid, *CSI* Caregiver Strain Index, *DNA* Deoxyribonucleic acid, *DTI* Diffusion Tensor Imaging, *ECG* electrocardiogram, *EDA* electrodermal activity, *EDTA* Ethylene Diamine Tetra Acid, *FLAIR* Fluid Attenuation Inversion recovery, *H&Y* Hoehn & Yahr, *IMU* Inertial Measurement Unit, *MDS-UPDRS-I/II/III/IV* Movement Disorders Society-sponsored revision of the Unified Parkinson’s Disease Rating Scale, non-motor experiences of daily living section (I), motor experiences of daily living section (II), motor examination section (III), and motor complications section (IV), *MMSE* Mini Mental State Examination, MoCa Montreal Cognitive Assessment, *MRI* Magnetic Resonance Imaging, *PASE* Physical Activity Scale for the Elderly, *PAX genes* Paired box genes, *PBMC* Peripheral Blood Mononuclear Cell, *PDQ-39* 39-item Parkinson Disease Questionnaire, *PPG* photoplethysmograph, *QSM* Quantitative Susceptibility Mapping, *QUIP-RS* Questionnaire for Impulsive-Compulsive Disorders in Parkinson’s Disease-Rating Scale, *RBD* Rapid eye movement sleep Behaviour Disorder, *RNA* Ribonucleic Acid, *SCOPA-aut* SCales for Outcomes in PArkinson’s disease, autonomic function section, *SCOPA-sleep* SCales for Outcomes in PArkinson’s disease, sleep section, *SF-12* 12-item Short Form, *STAI* State Trait Anxiety Inventory for Adults, *TUG* Timed Up and Go test

^a^Medical examinations & clinical assessments will be videotaped unless a subject declines; ^b^ ± 60 days; ^c^ within 4 weeks after each in-clinic visit

After each visit participants complete a set of validated questionnaires at home, including questionnaires about medication use, quality of life, lifestyle, neuropsychological symptoms, autonomic symptoms, sleep, and vision, among others [23–33]. These questionnaires are completed within 4 weeks after each visit, via an online survey module.

Finally, a copy of the medical record of the participant’s primary care physician is requested. This provides a rich information source of known and unknown markers of disease progression.

Participants are asked to wear the Verily Study Watch preferably 24/7, except during charging, for 2 years. During the baseline visit, the trial assessor discusses the importance of ambulatory monitoring with the subject and explains and demonstrates the use of the Study Watch. Moreover, a paper-based user manual is made available to each participant. The Verily Study Watch is an investigational, non-CE marked, multi-sensor wearable device designed to extend data collection for clinical studies beyond trial sites and into the free-living environment. For its use in the Personalized Parkinson Project approval is obtained by the Dutch Health and Youth Care Inspectorate. The device enables the collection of physiological and environmental data about acceleration/orientation, pulse rate, electrodermal activity (EDA), electrocardiogram (ECG), barometric pressure, relative humidity, environmental temperature, and ambient light level. The Verily Study Watch is intended for passive data collection only, with minimal information communicated to the user via the device (Fig. 1). Data from the Verily Study Watch are encrypted and sent securely to the Verily cloud using a USB syncing/charging cradle and wireless connectivity bridge (the Verily Study Hub). The Study Watch has been deployed in several studies, mainly in the United States, including the Baseline Health Study [34] and the Parkinson Progression Markers Initiative (PPMI) [5].

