### Statistical analyses

The primary objective of this study is to evaluate the rate of disease progression and, ultimately, to evaluate treatment response with respect to the presence of both established and potential biomarkers. More specifically, we will address two objectives in the short term:The individual associations between potential biomarkers and disease progression in Parkinson’s disease, with progression being expressed in terms of rate of decline in two key outcome domains of the disease, i.e., motor functioning and cognitive functioning.The prediction of disease progression after 1 year and 2 years on each of the two outcome domains.

Motor functioning will be determined using the score from the motor section (part III) of the Movement Disorders Society-sponsored revision of the Unified Parkinson’s Disease Rating Scale (MDS-UPDRS) [37], measured in the OFF state. Cognitive functioning will be determined using the score from the Montreal Cognitive Assessment scale (MoCA), a scale for global cognitive abilities that is validated for use in Parkinson’s disease [38].

For each of the two outcomes, the prediction will be made for absolute change scores (as a continuous measure) and clinically important change scores or clinically important threshold (as a dichotomous measure). For motor functioning, the dichotomous measure is a change of at least 5.5 [39, 40]. For cognitive functioning, the dichotomous measure is a follow-up score below 23.5 [41]. Both will be calculated over the first year of follow-up, as a measure for short-term disease progression (hence with direct clinical relevance for near-term treatment decisions), and over 2 years of follow-up, as a measure for mid-term prognosis.

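### Objective 1 names a rate of decline but models a change score without elapsed time, although visits may fall 60 days either side of target; the effect is small and cheap to remove

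*Protocol article*

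**What the plan says.** All references are to the protocol article.

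- **Visit timing.** In Table 1 the column "Visit 2 (1 Year)^b" carries footnote b, and so does the 2-year visit. The footnote reads "b^ ± 60 days; ^c^ within 4 weeks after each in-clinic visit".
- **Objective 1.** Statistical analyses describes individual associations between biomarkers and progression, with "progression being expressed in terms of rate of decline in two key outcome domains of the disease". The model paragraph then specifies a multivariable linear model for the change in the outcome. Age and disease duration are the only adjustment variables named.
- **Objective 2.** This is a separate aim: "The prediction of disease progression after 1 year and 2 years on each of the two outcome domains". Its continuous outcome is set by "the prediction will be made for absolute change scores (as a continuous measure". Its dichotomous outcomes are, for motor function, "For motor functioning, the dichotomous measure is a change of at least 5.5" and, for cognition, "the dichotomous measure is a follow-up score below 23.5". The same cuts serve both horizons ("Both will be calculated over the first year of follow-up", and again over 2 years). The text presents them as clinically important changes or thresholds.

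No stated outcome or model for these two objectives uses the actual time between baseline and follow-up visit.

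**The concern.** When every patient is seen at exactly the same interval, a change and a rate differ only by a constant, and the two words in objective 1 would be interchangeable. With a 120-day window they are different quantities. Two patients who decline at the same speed have different expected changes if one comes early and the other late. The objective 1 model as described has no term that absorbs this.

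At stake are some precision in the objective 1 associations, some date-dependence in the year-1 motor event, and clarity. The dataset is meant for sharing and, where predictors match, for validation in an outside cohort, so users need to know whether progression means change or change per unit of time.

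**Working it through.** **1. The plan's own figure.** Inputs from Sample size considerations: r = 0.2, two-sided alpha 0.05/110 = 0.00045, power 90%. With Fisher's z,

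n = ((3.506 + 1.282)/atanh(0.2))² + 3 = (4.788/0.2027)² + 3 ≈ 561.

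The article states 565, which agrees closely. Power at 565 is 90.3%. Enrolment: 565/0.87 = 649.4, stated as 650.

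**2. The window.** Year 1: 365 ± 60 gives days 305 to 425, ratio 425/305 = 1.39. Year 2: 730 ± 60 gives days 670 to 790, ratio 790/670 = 1.18.

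**3. The motor cut, assuming linear decline and no measurement error.** A patient losing 5.5 points/year scores 5.5 × 305/365 = 4.60 at the early edge (no event) and 5.5 × 425/365 = 6.40 at the late edge (event). The rate that just reaches 5.5 points is:

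| Visit | Early edge | On target | Late edge |
|---|---|---|---|
| Year 1 | 6.58/year | 5.50/year | 4.72/year |
| Year 2 | 3.00/year | 2.75/year | 2.54/year |

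**4. Size with realistic noise.** The article gives no rates or variances, so these are assumptions: change = b·t + e, with b normal (mean m of 2 to 5 points/year, between-patient SD s of 2 to 5), e normal (SD 5 to 7 points), and t uniform over the window. The SD of t is 120/√12 = 34.6 days = 0.0949 years, with variance 0.00901.

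Year-1 outcome variance, with a biomarker unrelated to timing:
- exact dates: s² + e²
- window ignored: s² + e² + 0.00901(m² + s²)
- actual interval as covariate: s² + e² + 0.00901·s²
- change divided by elapsed time: s² + e² × 365²/(305 × 425) = s² + 1.028·e²

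The design correlation of 0.2 shrinks by the square root of the ratio of the exact-date variance to each of the others. Example with m = 4, s = 4, error SD 5:

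| Analysis | Variance | Factor on r | Power at 565 |
|---|---|---|---|
| Exact dates | 41.00 | 1 | 90.3% |
| Window ignored | 41.29 | 0.9965 | 90.0% |
| Interval as covariate | 41.14 | 0.998 | 90.2% |
| Change ÷ time | 41.69 | 0.992 | 89.6% |

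Over the assumed range, power is 89.9 to 90.3% with the window ignored, 90.1 to 90.3% with the covariate, and 89.2 to 89.7% with division. Division loses because it inflates measurement error at early visits.

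**5. Event status (simulation, 1,000,000 patients per scenario).** About 1 to 3% of patients have a different year-1 motor status from the one they would have had on the exact date. At year 2 it is under 2%. In the example, event probability is 36.0% at day 305 and 45.1% at day 425, but that compares the two extreme days only. With a mean decline of 2 points/year, standardising the change to 365 days left year-1 classification equal or slightly worse in three of the four scenarios run.

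**6. If timing were related to a marker.** With an assumed marker–timing correlation of 0.3 in the example, the induced correlation with change is 0.3 × 4 × 0.0949/√41.3 ≈ 0.018, against the design target of 0.2.

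**The case against.** The strongest reply is that this is a condensed article, and how a change is derived from visit dates is usually left to an analysis plan, which is not shown. Nothing in the article says that actual dates will be ignored. That stands in part: the plan may already settle it. But the article is not merely silent. It names a rate as the target, a change as the dependent variable, and the covariates. Those statements need aligning whatever the plan says.

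Three stronger readings are tempting, and the documents do not support them.

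- *A reader might infer that the fixed 5.5-point cut contradicts the rate of decline.* It does not. The cut belongs to objective 2, which names no rate. It is offered as a clinically important change and used unaltered at both horizons. Asking whether a patient had worsened by that amount at the annual visit is a legitimate question. The cognitive cut is a state at follow-up, not a change.
- *A reader might infer that every patient declining by 4.72 to 6.58 points/year is classed by visit date.* That holds only without measurement error, and towards the ends of the range only for visits near a window edge.
- *A reader might infer bias towards severity-related markers because sicker patients come late.* The article says nothing on who comes late. It also describes hotel stays, visits spread over 1.5 days and a personal assessor, all of which work against delay from poor mobility.

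A practical objection also stands: the actual interval is unknown at baseline, so it cannot serve as an ordinary predictor in a prognostic model. The fix allows for this.

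**Conclusion.** The point holds as a minor inconsistency with an avoidable, small loss. Objective 1 is worded as a rate, its model uses a change, and no stated term accounts for follow-up that can differ by 120 days between patients. Under the assumed values the cost is less than 1 percentage point of power and about 1 to 3% of patients reclassified on the year-1 motor event. The planned 565 evaluable patients are unaffected.

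These sizes rest on linear decline, visit dates spread evenly over the window, and timing unrelated to biomarkers or progression. If timing is related to either, bias is possible, but the article gives no ground for assuming it.

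**What to change.** Keep the 60-day window and the 5.5-point cut. Under Statistical analyses, state the following.

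1. **Objective 1** uses actual time since baseline, either as a model-based slope or by adding the actual baseline-to-visit interval as a covariate to the change model. It should not divide each change by elapsed time.
2. **Objective 2** models include the actual interval when fitted and set it to the nominal 1 or 2 years when predicting.
3. An analysis with the motor change standardised to 365 or 730 days is at most a sensitivity analysis.

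The cost is a sentence or two of wording and one extra model term. The fix assumes that visit dates are recorded, which the existence of a window implies but the article does not state. The covariate recovers part or nearly all of the small loss, depending on how much rates vary between patients.
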